## Abstract

**Background:**

Men with localized prostate cancer often have unrealistic expectations. Practitioners are poor judges of men’s preferences, contributing to preference misdiagnosis and unwarranted practice variation. Patient decision aids (PtDAs) can support men with decisions about localized prostate cancer. This is a comparative case study of two strategies for implementing PtDAs in clinical pathways for men with localized prostate cancer, evaluating (a) PtDA use; (b) impact on men, practitioners, and health system outcomes; and (c) factors influencing sustained use.

**Methods/design:**

Guided by the Knowledge to Action Framework, this comparative case study will be conducted using administrative data, interviews, and surveys. Cases will be bound by geographic location (one hospital in Ontario; province of Saskatchewan) and time. Eligible participants will be all men newly diagnosed with localized prostate cancer, with outcomes assessed using administrative data and interviews. Nurses, urologists, radiation oncologists, and managers will be surveyed and a smaller sample interviewed. Cases will be established for each setting with findings compared across cases. Changes in the proportions of men given the PtDA over 2 years will be determined from administrative data. Factors associated with receiving the PtDA will be explored using multivariable logistic regression analysis. To assess the impact of the PtDA, outcomes will be described using mean and standard deviation (men’s decisional conflict) and frequency and proportions (practitioners consulted, uptake of treatment). To estimate the effect of the PtDA on these outcomes, adjusted mean differences and odds ratios will be calculated using exploratory multivariable general linear regression and binary or multinomial logistic regression. Factors influencing sustained PtDA use will be assessed using descriptive analysis of survey findings and thematic analysis of interview transcripts.

**Discussion:**

Determining how to embed PtDAs effectively within clinical pathways for men with localized prostate cancer is essential. PtDAs have the potential to strengthen men’s active role in making prostate cancer decisions, enhance uptake of shared decision-making by practitioners, and reduce practice variation. Our team of researchers and knowledge users will use findings to improve current PtDA use and consider scaling-up implementation.

**Electronic supplementary material:**

The online version of this article (doi:10.1186/s13012-016-0451-1) contains supplementary material, which is available to authorized users.

## Background

Although patient decision aids (PtDAs) are effective interventions for translating evidence for patients [1], they are not routinely used in clinical practice [2]. Our study aims to close the gap between what is currently known about PtDAs from research studies and what is done with PtDAs when they are implemented in routine clinical practice. Men with localized prostate cancer face a difficult decision because there are four main options (e.g., surgery, external radiation, brachytherapy, and active surveillance) with different potential benefits and harms. Given little evidence to indicate that one option is better than another, the chosen option should be consistent with men’s informed preferences based on weighing benefits and harms across options [3–5].

When asked to take an active role in making these difficult decisions, patients often experience decisional conflict and have unrealistic expectations [6–9]. Decisional conflict is “personal uncertainty about which course of action to take when choice among competing options involves risk, regret, or challenge to personal life values” [7–9]. Adults with unresolved decisional conflict are more likely to delay decisions, feel regret, be dissatisfied, and blame doctors for bad outcomes [10, 11]. Moreover, without effective decision support, patients may be exposed to more costly options without any better outcomes [12, 13]. Studies in Canada and the USA found that urologists and radiation oncologists often provide unbalanced information on options in favour of their own expertise, and they are not able to correctly guess men’s preferences [14, 15]. Practice variations in age-standardized rates of surgery for prostate cancer are 32 to 57 % across Ontario, Canada [16]. This variation may be unwarranted given that the best option depends on men’s preferences [17].

For adults facing difficult decisions, providing a structured approach to decision-making such as PtDAs helps empower individuals, resolves decisional conflict, and reduces unwarranted practice variation [13, 17]. PtDAs are booklets and/or videos that provide balanced information on options (benefits/harms), help clarify patients’ preferences, and guide patients making decisions with their practitioner [18]. A systematic review of 115 trials of PtDAs (including prostate cancer treatment) found that patients exposed to PtDAs are more involved in decision-making with improved knowledge, more realistic expectations of outcomes, and enhanced agreement between options chosen and patients’ values [13, 19]. Despite strong evidence, few PtDAs are used in clinical practice [2]. In 17 implementation studies, factors interfering with their use were healthcare professionals having inadequate training, being indifferent about using them, lacking confidence in their content, and being concerned about disrupting workflows [2]. Only one implementation study in England involved men with prostate cancer [20]. These men had improved knowledge and values-choice agreement, shifted rates from surgery to radiation, and rated the PtDA positively. Staff said the PtDA was used by men at home and off-loaded work in busy clinics. Other studies have shown that few practitioners attempt to involve patients in decision-making and fewer adjust care to patients’ preferences [21], thus leading to a “silent misdiagnosis of clients’ preferences,” a key determinant of health system performance as a whole [22]. Hence, it is important to study implementation of PtDAs to understand approaches that increase sustained use and have positive impacts on patient, practitioner, and health system outcomes.

In our previous research with 192 patients in an ambulatory oncology program, only half were offered treatment choices and those offered choices were more likely to have an active role in decision-making [23]. Patients whose preferred role was different from their actual role preferred more involvement. Next, we explored using PtDAs for men with localized prostate cancer [24]. A team of researchers and knowledge users appraised PtDAs against the International Patient Decision Aid Standards [25] to identify two higher quality PtDAs (one was booklet only; one was booklet plus video). Interviews with prostate cancer survivors, urologists, oncologists, and nurses rated the PtDAs positively for plain language, helpful information, and ability to share with family [24]. Men wanted more information on sexual effects and brachytherapy. Factors perceived to influence their use were men’s preferred level of involvement, staff time to distribute, practitioners’ own agenda, and practitioner/manager buy-in. Since September 2010, the higher quality PtDA with booklet and video from Health Dialog was integrated into the clinical pathway for men diagnosed with localized prostate cancer at The Ottawa Hospital. In 2010, a key health goal of Saskatchewan was to implement a shared decision-making framework to engage patients in decisions about their treatment options [26]. In May 2013, the prostate cancer surgical pathway in Saskatchewan started using PtDAs with men having localized prostate cancer [27]. Implementation has not been evaluated in either program and anecdotally, not all men receive a PtDA.

Researchers on this team have also updated the Cochrane review of PtDAs [13], the Cochrane review of interventions for uptake of shared decision-making [28], and reviews on shared decision-making training [29–31], PtDA implementation [2], and PtDA used with decision coaching [32, 33]. None of the studies measured sustained the use of PtDAs or factors influencing sustained use. A recent study of PtDA implementation for patients with cystic fibrosis in Canada revealed 85 and 92 % PtDA usage at 1 and 2 years, respectively, but findings were based on nurse reporting rather than more objective administrative data [34].

The overall aim of this comparative case study is to evaluate two strategies for implementing PtDAs in clinical pathways for men with localized prostate cancer by measuring (a) the use of PtDA over a 2-year period after implementation; (b) impact of the PtDA on men, practitioners, and health system outcomes; and (c) factors influencing sustained use (or not) for each strategy.

## Methods/design

Our comparative case study will use mixed methods and will be guided by the Knowledge to Action Framework [35, 36]. Following Yin’s approach, the cases will be bound by location (prostate cancer clinical pathway at one hospital in one provincial health system and the prostate cancer surgical pathway in another province) and time period (2 years after PtDA implementation) [37]. The Knowledge to Action framework focuses on specific implementation factors essential for success in real world, naturalistic environments [35, 36]. The Action Cycle was activated by a problem identified by the knowledge users (e.g., men want to be more involved in prostate cancer decisions), and the knowledge solution is a PtDA. Then, we will identify interventions to overcome identified barriers. This proposed implementation study is focused on the final phases of the Framework: monitor use, evaluate outcomes, and measure sustained use. Sustainability requires monitoring use for 2 or more years [38]. We obtained ethics approval at The Ottawa Health Science Network Research Ethics Board (#20150604-01H), the Saskatoon Health Region Research Ethics Board (#BEH-15-382), Reginal Qu’Appelle Health Region Research Ethics Board (REG-15-125), and the University of Saskatchewan Behavioural Research Ethics Board (BEH#15-382).

The *setting* for our study is prostate cancer healthcare services that implemented PtDAs in the clinical pathways: The Ottawa Hospital in Ontario (in 2010) and the Ministry of Health in the Province of Saskatchewan (in 2013). These prostate cancer healthcare services have urologists and radiation oncologists serving populations of about 1 million each. Annually, about 400 men have consultations for prostate cancer at The Ottawa Hospital Cancer Assessment Clinic and about 600 in Saskatchewan. Within the clinical pathway, men diagnosed with localized prostate cancer are asked to use the PtDA at home in preparation for the consultation. Nurses, trained in interprofessional shared decision-making [31], discuss men’s questions prior to the physician consultation.

*Participants* for the interviews are men who have received a diagnosis of localized prostate cancer (including their partners) and received services at The Ottawa Hospital or in Saskatchewan. Other stakeholder participants who have varying levels of influence in the prostate cancer programs include urologists, radiation oncologists, nurses, and managers.

*Procedures* focus on collecting clinical administrative data (clinical databases, electronic/paper-based health records) and conducting a survey and interviews (Table 1). Routinely collected administrative data sources will be reviewed to identify men newly diagnosed with localized prostate cancer for calendar years of 2011–2012 in Ottawa and 2014–2015 in Saskatchewan. Data will be retrieved on (a) their age, co-morbidities with severity, prostate cancer characteristics; (b) practitioners’ documentation of the decision-making consultation; (c) uptake of treatment or surveillance; (d) whether given the PtDA or not; and (e) level of decisional conflict (Table 2).

**Table 1 Tab1:** Proposed study data collection elements and analysis

Outcome	Participants	Data source	Analysis
Proportion given the PtDA	Men with localized prostate cancer	Clinical administrative^a^ data (~*n* = 1000)	Proportion with 95 % confidence intervals for each case study
Men’s outcomes: decisional conflict	Men with localized prostate cancer	Clinical administrative^a^ data (~*n* = 1000)	Linear regression (decisional conflict) to compare those who were given the PtDA to those who were not
Practitioner’s outcome: factors influencing PtDA use	Urologists, radiation oncologists, and nurses in prostate programs	Mailed survey (~*n* = 40)	Multivariable ordinal logistic regression analysis of practitioner’s reported use of PtDA with factors reported in the survey as covariates. Subgroup analysis will be done by types of practitioner (e.g., urologists, radiation oncologists, nurses)
Health system outcomes: uptake of treatment (including surveillance) and practitioner consultations	All men with localized prostate cancer	Clinical administrative^a^ data (~*n* = 1000)	Multinomial and binary logistic regression analysis of treatment uptake and practitioner consultations with receipt of the PtDA as main predictor, and adjusting for patient demographic and clinical characteristics.
Factors influencing PtDA implementation	Key stakeholders in each program	Individual interviews (~*n* = 30–40)	Thematic analysis guided by the Knowledge to Action Framework

^a^Clinical administrative data for all men for 2-year period after implementing the PtDA

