**Table 2 Tab2:**
[figure not shown]
Data collection tool: prostate cancer PtDA implementation study

A survey will be sent to urologists (*n* = 8–10) per site, radiation oncologists (*n* = 5-7), and nurses (*n* = 4–6) in the prostate programs to assess their use of PtDA and factors influencing use. Eligible participants will receive a mailed package that will include a cover letter with the study purpose and information on how the information will be used and the survey with a stamped pre-addressed envelope. To enhance response rates, Dillman’s approach will be used with reminders at 2, 4, and 5 weeks [39].

Interviews will be conducted with a purposeful sample of men given/not given the PtDA (and/or their partners), nurses, managers, radiation oncologists, and urologists in each program (Table 1). Men newly diagnosed with prostate cancer during the last 3 years post-PtDA implementation will be contacted by a healthcare professional from the circle of care or through the local prostate cancer support groups. Purposeful sampling will be used to identify other stakeholders having varying levels of influence in the prostate cancer programs (e.g., nurses, urologists, radiation oncologists, and managers). Prospective participants will be invited to participate in an interview by (a) announcement of the study at staff meetings, (b) hard copy posters on staff bulletin boards, and (c) email to staff (Ottawa only). A letter explaining the study will be provided to prospective participants, and written informed consent will be obtained (Additional files 1 and 2). For healthcare practitioners, a semi-structured interview guide developed using the Knowledge to Action Framework [35] will be used to explore perceptions of PtDAs, factors influencing PtDA sustained use, interventions required to overcome remaining barriers, and concurrent initiatives that may have influenced PtDA use. For men given or not given a PtDA, a semi-structured interview guide was developed to learn more about their experience with how the decision was made to treat or monitor their prostate cancer. All participants will be asked to complete demographic questions.

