### Analysis

Two cases will be developed with a rich description of the context and outcomes with comparisons within and across the cases [37]. For PtDA use, the proportion of men given the PtDA will be calculated for each site with 95 % confidence intervals (Table 1). We anticipate about 600 men diagnosed with localized prostate cancer over 2 years at The Ottawa Hospital Cancer Assessment Clinic and 400 in the Provincial Prostate Pathway in Saskatchewan. Using conservative estimates for proportions given the PtDA of 50 and 90 % in Ottawa and Saskatchewan, respectively, these sample sizes are adequate to estimate the true proportions given the PtDA with margins of error +4.0 % in Ottawa and +2.9 % in Saskatchewan using two-sided 95 % confidence intervals. Characteristics and outcomes of patients who did and did not receive the PtDA will be described at each site using mean and standard deviation for continuous variables, and frequencies and proportions for categorical variables.

Factors associated with receiving the PtDA will be explored at each site and overall using multivariable logistic regression analysis by entering patient characteristics (e.g., age, co-morbidity, severity of disease, cancer characteristics) as well as provider characteristics (e.g., sex, years of experience, discipline). To explore differences in the effect of these characteristics across the two sites, site and interactions between the characteristics and site will be included in the model. If the proportion using the PtDA is 50 % in Ottawa and 90 % in Saskatchewan, according to a commonly used rule of 10 events per independent variable, the maximum number of variables that can be included in these analyses is 66; thus, we have more than the required degrees of freedom available to fit our models. The extent of missing data will be tabulated, and characteristics of those with and without missing data will be compared. If more than 5 % missing data is observed among predictors, the use of multiple imputation will be explored. The analysis will account for clustering by provider through the inclusion of random intercepts for each provider. The model will be estimated using pseudo-likelihood or maximum likelihood in SAS v9.3.

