Outcomes between those given the PtDA and those not given it will be described at each site using mean and standard deviation (decisional conflict) and frequency and proportions (uptake of treatment, type of practitioner consulted). To estimate the effect of the PtDA on these outcomes after accounting for potential confounders, we will conduct exploratory multivariable general linear regression and binary or multinomial logistic regression at each site and overall. The analysis will adjust for patient characteristics associated with the use of the PtDA, and patient clinical and demographic characteristics potentially associated with the outcomes. To explore differences between the sites, we will include site and its interaction with the receipt of the PtDA into the model. Results will be expressed as adjusted mean differences and adjusted odds ratios together with 95 % confidence intervals.

For impact on practitioner outcomes and sustained use, we will identify remaining barriers influencing practitioner PtDA use with the survey and interview data. Audio-taped interviews will be transcribed verbatim and analyzed qualitatively by two team members using thematic analysis. We expect to reach saturation by 12 to 15 interviews in each case study [48].

The study *Timeline* is 12 months: 3 months for start-up; 5 months for collecting clinical administrative data, conducting the survey, and interviewing; 2 months for data cleaning/analysis; and 2 months for drafting case studies and disseminating findings.

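### The survey regression in Table 1 has no stated site term or by-site analysis, so a factor that merely differs between Ottawa and Saskatchewan can look like an influence on PtDA use

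*Protocol article*

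**What the plan says.** The aim at the end of the Background asks, under (c), for "factors influencing sustained use (or not) for each strategy". Each strategy belongs to one site, so strategy and site coincide.

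Table 1 (Methods/design) gives the practitioner row its data source, "Mailed survey (~*n* = 40", and its analysis: "Multivariable ordinal logistic regression analysis of practitioner’s reported use of PtDA with factors reported in the survey as covariates". One split is named: "Subgroup analysis will be done by types of practitioner (e.g., urologists, radiation oncologists, nurses". The text after Table 2 gives the mailing numbers: "A survey will be sent to urologists (*n* = 8–10) per site, radiation oncologists (*n* = 5-7), and nurses (*n* = 4–6".

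The regressions on men's data are treated differently. In the Analysis section they are run site by site and combined. For receipt of the PtDA, "site and interactions between the characteristics and site will be included in the model". For the outcome models, "we will include site and its interaction with the receipt of the PtDA into the model".

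The remaining text on the survey gives no site handling. The Analysis section says that remaining barriers will be identified from survey and interview data, and the Abstract announces a descriptive survey analysis.

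**The concern.** Site is the unit that the study compares, and it may be related to both sides of this regression. Reported use may differ by site. So may the survey factors: implementation began in 2010 in Ottawa and 2013 in Saskatchewan, one setting is a hospital clinic and the other a provincial pathway, and the protocol itself notes that barriers can change as PtDAs are used. If both differ, a model without site attributes part of the site difference in use to any factor whose level happens to differ.

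The result feeds into action. The Interventions paragraph calls for interventions against barriers when use is below 80 %, and for monitoring otherwise. If that rule is applied by site, the planning figures of 50 % and 90 % put the two sites on opposite sides of it. A single coefficient over both sites does not show whose barriers it describes.

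**Working it through.** **1. Does about 40 mean both sites?** Reading the per-site label as covering all three professions:

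- minimum per site: 8 + 5 + 4 = 17
- maximum per site: 10 + 7 + 6 = 23
- two sites: 34 to 46, midpoint 40

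This reproduces the figure in Table 1. If the label covered urologists only, the total would be 2 × 8 + 5 + 4 = 25 to 2 × 10 + 7 + 6 = 33, which does not reach 40. The row therefore counts both sites, with about 20 practitioners each before non-response.

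**2. Site figures.** The Analysis section plans with 50 % of 600 men in Ottawa and 90 % of 400 in Saskatchewan. The half-widths 1.96 × √(0.5 × 0.5 / 600) = 4.0 % and 1.96 × √(0.9 × 0.1 / 400) = 2.9 % match the stated margins, so the pairing of figure and site is clear. The site odds ratio is (0.9/0.1) / (0.5/0.5) = 9, a log odds shift of ln 9 = 2.2.

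**3. Simulation.** Assumptions: 20 practitioners per site; a three-level use scale; the probability of the top level 50 % at one site and 90 % at the other (the men's figures applied to practitioners); and a normally distributed factor with no effect within either site, whose mean differs between sites by d SD. A proportional-odds model was fitted with and without a site term. The factor was tested by likelihood ratio at two-sided 5 %, in about 300 runs per scenario.

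| Top-level use by site | d | Rejected, no site term | Rejected, with site term |
|---|---|---|---|
| 50 % v 90 % | 0 | 5.7 % | 6.1 % |
| 50 % v 90 % | 0.5 | 9.0 % | 6.4 % |
| 50 % v 90 % | 1.0 | 26.3 % | 5.3 % |
| 50 % v 75 % | 0.5 | 9.3 % | 8.0 % |
| 50 % v 75 % | 1.0 | 14.0 % | 8.3 % |
| equal | 0.5 | 6.3 % | 7.0 % |
| equal | 1.0 | 6.0 % | 4.3 % |

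At 50 % v 90 %, the median log odds ratio for the inert factor without site was 0.22 (d = 0.5) and 0.40 (d = 1.0). With site it was 0.01 and 0.00.

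**4. Second simulation.** This added one unrelated covariate and used 500 to 1000 runs. At 50 % v 90 % it gave, without v with site:

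- d = 0.5: 12 % v 7 %
- d = 0.8: 18 % v 6 %
- d = 1.0: 22 % v 8 %

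Variations at d = 0.8:

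- 17 per site: 16 % v 7 %
- 23 per site: 20 % v 6 %
- 12 respondents per site: 16 % v 7 %
- five-level use scale: 27 % v 6 %
- smaller site gap in use (log odds shift 1.1): 11 % v 5 %

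**5. Reading.** In the three-level scenarios at 50 % v 90 % with 20 per site, the range is about 9 to 26 % without site and about 5 to 8 % with it. Monte Carlo error is about 1 to 2.5 points, so the inflation at 0.5 SD is small. There is no material inflation unless both use and the factor differ by site.

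**The case against.** The strongest reply is that Table 1 is shorthand. Its rows for decisional conflict and treatment uptake also omit site and also give a two-site total, about 1000, yet the Analysis section runs those models by site. Pooling of the survey model is thus inferred, not stated. That is correct, and a reader should not infer that the protocol rules site out. The difference is that for the men's models the text supplies what the table omits. For the survey it supplies nothing, while the table does name both a covariate set and a split. A condensed article may leave out a full covariate list, but here it gives a specification that leaves out the study's main comparison.

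Other objections narrow the point:

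- The words "Using conservative estimates for proportions given the PtDA of 50 and 90 % in Ottawa and Saskatchewan, respectively" concern men given the PtDA and serve sample-size reasoning. They do not forecast practitioner-reported use.
- The SD differences are assumed, and the protocol has no significance rule for choosing barriers. The rejection rates therefore measure how misleading the associations could be, not the error rate of a planned decision. Barriers are also to be drawn from survey and interviews together.
- A factor that is constant within a site, such as a provincial mandate, is fully aliased with site. A site term removes it and cannot say whether it matters.
- A site term does not reveal a factor that matters at one site only. That would need interactions or separate models, which about 20 per site cannot support.

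**Conclusion.** The point holds in a limited form. The stated survey regression covers both sites by the protocol's own counts, names no site term and is split only by profession, unlike the regressions on men's data. It can therefore mistake a site difference for a factor effect. The illustrative size is about 9 to 26 % false positives against about 5 to 8 % with a site term, conditional on a 0.5 to 1.0 SD site difference in the factor and on the men's 50 % and 90 % holding for practitioners. With a smaller gap in use the inflation shrinks, and with no gap it is not material.

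A reader might go further and infer that aim (c) goes unanswered for each strategy. The document does not support that. Interviews are held in each program with 12 to 15 expected per case, and findings are compared within each case and between the two. What is missing is an answer by strategy from the stated survey regression. The descriptive survey analysis in the Abstract does not supply it either, since no split by site is named there.

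**What to change.** Amend the practitioner row of Table 1 as follows:

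- Report practitioner-reported use and each survey factor descriptively for Ottawa and for Saskatchewan, as the primary survey result.
- Include site as a covariate in any association model that combines the sites.
- Make profession a secondary description. With 4 to 10 people mailed per profession and site, it supports no more than that.
- Do not run separate regressions by site or site interactions at about 20 per site.
- State that factors constant within a site cannot be separated from the implementation strategy itself.

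The same edit can align Table 1 with the Abstract, which describes the survey analysis for aim (c) as descriptive only.

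The cost is one degree of freedom and wider intervals for factors that differ mainly between sites. No new data are needed, because the survey is already mailed by site. The change does not recover factors that act at one site only; for those, the by-site descriptions and the interviews remain the source.

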*Interventions* will be identified to address barriers interfering with the use of PtDAs if the prevalence of use is found to be less than 80 %. If PtDA use is 80 % or higher, strategies for monitoring sustained use with feedback mechanisms will be established [40]. Successful implementation of evidence in clinical practice requires tailored interventions based on identified barriers [41].

*Instruments* to be used have been found to be valid, reliable, and have been previously been used in PtDA studies. The four-item SURE test is used to screen for decisional conflict to inform clinical practice [42–44]. It has moderate reliability (Cronbach Alpha 0.65) and discriminates between those who had/had not made a choice. Factors influencing PtDA use by practitioners will be measured using the 12-item Continuing Professional Development Reaction Questionnaire (Cronbach Alpha 0.77-0.85) [45]. Potential environmental barriers influencing PtDA use will be taken from a Barriers Survey [46].

*Outcomes* are based on the Knowledge to Action Framework [35]. After knowledge is implemented (e.g., PtDA), its uptake should be monitored to determine how and to what extent it is used [35]. We plan to use administrative data to measure the proportion of men who were given the PtDA and qualitative interviews to explore men’s use. The next phase of the Framework is to measure the impact of knowledge use on outcomes specific to patients, providers, and healthcare systems [35]. We will measure the impact of PtDA use on men’s decisional conflict using administrative data; practitioners’ and patients’ consultations using qualitative interviews; and impact on healthcare systems using administrative data to measure uptake of treatment and types of practitioners consulted during decision-making. Measuring impact of PtDA on these outcomes will ensure that PtDA use is influencing quality indicators as observed in randomized controlled trials without any unintended consequences [13, 40]. Sustaining the use of the knowledge is the last phase in the Action Cycle of this Framework [35, 47]. Given that barriers can change with PtDA use [46], we will assess barriers using a practitioner survey and qualitative interviews.

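### Table 1's multivariable ordinal regression of about 40 practitioner surveys sets no covariate limit, cannot support multivariable results by practitioner type, and does not match the abstract's descriptive analysis

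*Protocol article*

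**What the plan says.** Table 1, in the row for the practitioner outcome, gives the data source as "Mailed survey (~*n* = 40" respondents. The planned analysis is a multivariable ordinal logistic model; its outcome, covariates and subgroups are given as "reported use of PtDA with factors reported in the survey as covariates. Subgroup analysis will be done by types of practitioner".

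The survey paragraph of Methods/design says who is mailed: "A survey will be sent to urologists (*n* = 8–10) per site, radiation oncologists (*n* = 5-7), and nurses (*n* = 4–6". Reminders are planned, but no expected response rate is given.

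The Instruments paragraph names the source of the factors: "Factors influencing PtDA use by practitioners will be measured using the 12-item Continuing Professional Development Reaction Questionnaire". Environmental barriers are added from a separate Barriers Survey, whose number of items is not given.

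The Analysis section applies a rule of 10 events per independent variable, but only to the patient-level model of who received the decision aid. For the survey it names no regression; it says only that remaining barriers will be identified from survey and interview data.

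The abstract says: "Factors influencing sustained PtDA use will be assessed using descriptive analysis of survey findings and thematic analysis of interview transcripts".

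**The concern.** The article checks model size where there are about 1000 records and room to spare, but not where there are about 40. Table 1 places no limit on how many survey factors enter the model, and it adds analysis by practitioner type in groups of 8 to 20 people. Followed with most of the questionnaire items as covariates, the pooled model would be overfitted: its odds ratios would be unstable and too often nominally significant. Within a practitioner type, a model with that many covariates would often have no finite estimates.

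Factors influencing sustained use are one of the three stated aims. The article also says that interventions will address barriers if use is below 80%, so spurious survey associations could colour that choice. Finally, the abstract and Table 1 describe different analyses of the same survey, and a reader cannot tell which one is planned.

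**Working it through.** **1. Survey size.** Inputs are the counts in the survey paragraph, read as per site for every type.
- Per site: 8 + 5 + 4 = 17 to 10 + 7 + 6 = 23.
- Two sites: 34 to 46, midpoint 40. This reproduces Table 1.
- If per site applied to urologists only: 16 + 5 + 4 = 25 to 20 + 7 + 6 = 33, which does not give 40.

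So the 40 is the number mailed, with nothing taken off for nonresponse. By type over two sites: urologists 16–20, radiation oncologists 10–14, nurses 8–12.

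**2. The protocol's own rule.** For the patient-level model: (600 × 0.50 + 400 × 0.90) / 10 = 660 / 10 = 66 variables, as the Analysis section states.

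**3. The same rule applied to the survey.** For an ordinal outcome the effective size is n − (1/n²) Σ nⱼ³, where nⱼ is the number in category j. The split of reported use is not given, so several are assumed. With all 40 responding:
- five equal categories: 40 − 5 × 8³ / 40² = 38.4, or 3.8 covariates;
- three equal categories: 40 × (1 − 1/9) = 35.6, or 3.6 covariates;
- split 10/20/70%: 40 × (1 − 0.352) = 25.9, or 2.6 covariates;
- only two equal categories, counting 20 events directly: 2.0 covariates.

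Covariates supported over the same splits:

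| Group | n | Covariates at 10 per variable |
|---|---|---|
| All, full response | 40 | 2.0–3.8 |
| All, assumed 70% response | 28 | 1.4–2.7 |
| Urologists, full response | 16–20 | 0.8–1.9 |
| Radiation oncologists, full response | 10–14 | 0.5–1.3 |
| Nurses, full response | 8–12 | 0.4–1.2 |

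A multivariable model needs at least two covariates, and no practitioner type reaches two even at full response. Covariate-by-type interactions in one pooled model would need at least as many parameters as separate models, so they do not avoid the limit.

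**4. What overfitting would look like.** These are proportional-odds simulations with no true association; the larger two assumed four equal outcome categories and a covariate correlation of 0.3.
- n = 40, 12 covariates: the global test was falsely significant in 17% (60 runs), 17.5% (600 runs) and 21% (300 runs), against a nominal 5%.
- n = 28, 12 covariates: 26% (300 runs).
- n = 40, 4 covariates: about 8%. With 3 covariates: 4%.

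**5. Whether the model can be fitted.** This is a separation check by linear programming, with 300 runs per setting, a four-category outcome, covariate correlation 0.3 and one modest effect. The table gives the share of runs with no finite maximum likelihood estimate.

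| n | 3 covariates | 5 covariates | 12 covariates |
|---|---|---|---|
| 40 | 0% | 0% | 0% |
| 20 | 0% | 0% | 28% |
| 16 | 0% | 1% | 89% |
| 14 | 0% | 4% | 98% |
| 12 | 0% | 9% | 100% |
| 10 | 6% | 30% | 100% |
| 8 | 21% | 76% | 100% |

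The pooled model can be fitted at n = 40 even with 12 covariates, at about 40 / 12 = 3.3 respondents per covariate. Within types, failure depends strongly on how many covariates enter.

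**6. The two statements of the analysis.** The abstract sentence concerns factors influencing sustained use, and the Table 1 row concerns factors influencing use. There is only one practitioner survey, and the Analysis section treats practitioner outcomes and sustained use together. The two descriptions therefore cover the same data and need to agree.

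**The case against.** The strongest reply is that the covariate count is not in the document. Table 1 refers to factors, not to all 12 items entered singly. The Instruments paragraph reports reliability as a range (0.77–0.85), which suggests several multi-item scales whose scores could be the covariates. The choice of scores may properly sit in a fuller plan. This stands in part: a pooled model with two to four scores is workable at n = 40, and steps 4 and 5 show it behaving acceptably. It does not help the practitioner types, where fewer than two covariates are supportable however the items are scored.

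A reader might infer that the full model will be refitted in each practitioner type and is bound to separate. The document does not say so. It promises subgroup analysis without defining it, and descriptive or single-factor results by type would fit the wording. Near-certain separation arises only with many covariates in the smaller groups.

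A reader might also infer that the regression alone selects the barriers to be targeted. It does not. Barriers are to be identified from the survey and from about 30–40 interviews, and the trigger for intervention is prevalence of use, not an odds ratio.

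Lastly, an abstract condenses, and descriptive summaries and a regression can both be reported. The mismatch calls for alignment and is not proof of two incompatible plans.

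**Conclusion.** The point holds at moderate severity. As written, Table 1 commits to a multivariable ordinal regression with no covariate limit on a sample that is about 40 only if everyone responds. The protocol's own rule allows about 2 to 4 covariates pooled, fewer after nonresponse, and fewer than two in any practitioner type. A multivariable model by type is not supportable. The pooled model is not impossible; it lacks a limit, and with 12 covariates its global test would be falsely positive about 17–21% of the time.

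The survey size, the counts by type and the 66 come from the document. The outcome split, the 70% response, the covariate correlation and the figure of 12 entered covariates are assumptions. The limits on model size hold across all the splits shown; the false-positive figure holds only if all 12 items are entered.

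The severity is no higher because the survey is a secondary component, interviews also inform the barriers, and the patient-level analyses on about 1000 records are untouched.

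**What to change.** Change the Table 1 entry so that the survey analysis is primarily descriptive: item and scale-score summaries, with unadjusted associations with reported use. Make results by practitioner type and by site descriptive only. If a regression is kept, limit it to one pooled model with at most two or three pre-chosen scale scores, labelled exploratory. Align the abstract and the Analysis section with whichever version is adopted, and say that the 40 is the number mailed and not the expected number of returns.

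The change is to one table cell and a sentence or two of text. What is given up is adjusted odds ratios for many factors and by practitioner type, which these data could not support.
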